### Statistical analysis

Baseline characteristics of index patients and first degree relatives will be reported for intervention and control groups. *Aim 1*. The proportion of index patients and the proportion of first degree relatives who undertake screening/surveillance tests in line with NHMRC recommendations for their risk category in years 1, 2 and 3 following diagnosis in the index case will be compared between the two experimental groups using the chi-square test. *Aim 2*. Sociodemographic characteristics, screening history, risk status, concurrent engagement in alternative programs of surveillance and symptom status, of those who are appropriately and inappropriately screened at each time point will be compared using the chi-square test for categorical variables and the t-test or a non-parametric equivalent for continuous variables. Logistic regression will then be used to examine factors associated with appropriate screening/surveillance while adjusting for potential confounders. Variables will be included in the initial logistic model if they have a p value of 0.2 or less on univariate analyses, with backward stepwise methods used to exclude variables with a p value of 0.10 or more on the likelihood ratio test. Analysis will be undertaken separately for the index cases and for first degree relatives. Analyses will be adjusted for clustering of relatives within index patients using Generalised Estimating Equations.

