**Methods/Design:**

A randomized controlled trial will be used to test the effectiveness of a print-based intervention to improve adherence to colonoscopy surveillance among people with CRC and adherence to CRC screening recommendations among their first degree relatives (FDRs). People diagnosed with CRC in the past 10 months will be recruited through a population-based cancer registry. Consenting participants will be asked if their first degree relatives might also be willing to participate in the trial. Information on family history of CRC will be obtained from patients at baseline. Patients and their families will be randomized to either minimal ethical care or the print-based intervention. The print-based intervention for FDRs will be tailored to the participant's level of risk of CRC as determined by the self-reported family history assessment. Follow up data on surveillance and screening participation will be collected from patients and their FDRs respectively at 12, 24 and 36 months' post recruitment. The primary analyses will relate to comparing levels of guideline adherence in usual care group versus print-based group in the patient sample and the FDR sample respectively.

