### Setting

People with a diagnosis of bowel cancer within the last 10 months will be recruited from population-based cancer Victorian Cancer Registry covering the entire Australian state of Victoria (population 5.5 million).

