### Patient eligibility and recruitment

People with bowel cancer (index cases) who meet the following criteria will be identified from the cancer registry: 1) aged 18 or older; 2) registered with cancer registry within 10 months of diagnosis. The registry will write to the notifying doctor of each potentially eligible person and ask the doctor to contact the registry within 4 weeks if there is any reason why the patient should not be contacted about the study. Index cases whose doctors perceive them to be unsuitable for the study will be excluded. The registry will contact remaining index cases and ask their permission to pass their contact details onto the research team. Two reminders will be sent to non responders. Those who consent will be invited to participate in the trial with two reminders sent to non responders.

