### Follow up assessments

Both first degree relatives and patients will be mailed follow up surveys at 12, 24 and 36 months. First degree relatives will be asked to provide self report information on the type of bowel cancer screening undertaken in the past 12 months (if any), and any days off work due screening. Patients will be asked to provide self report information about participation in surveillance colonoscopy within the past 12 months, quality of life. Patients or first degree relatives who report having had a colonoscopy or bowel cancer screening test in the past 12 months will be asked for permission to contact their doctor to verify the timing and results of the test. A random sample of 10% of self reported screening will be verified in this way to determine accuracy of self reported screening behavior.

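### The Aim 1 outcome is defined by year since the index case's diagnosis but collected and powered from recruitment, so part of year 1 can precede randomization and the years do not match the surveys

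*Protocol article*

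**What the plan says.** **Analysis clock.** Under Statistical analysis, Aim 1, the proportions of index patients and of relatives tested in line with the guideline are compared by chi-square test "in years 1, 2 and 3 following diagnosis in the index case".

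**Data clock.** The abstract (Methods/Design) places follow-up "at 12, 24 and 36 months' post recruitment". Follow up assessments gives the same times without restating the origin: "Both first degree relatives and patients will be mailed follow up surveys at 12, 24 and 36 months". Patients report "participation in surveillance colonoscopy within the past 12 months", and relatives report screening over the same look-back period. The Sample size section sets its numbers available, differences and power at the 12, 24 and 36 month follow-ups.

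**Distance between the clocks.** Setting reads "People with a diagnosis of bowel cancer within the last 10 months will be recruited", and the abstract agrees. Patient eligibility and recruitment applies the limit to a different event: "registered with cancer registry within 10 months of diagnosis". After that come a 4-week period for the doctor to object, registry contact with two reminders, and a trial invitation with two reminders. Consenting patients and relatives are then randomized as a family unit (Randomization).

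**The concern.** For anyone who enters some months after diagnosis, the first year since diagnosis and the first year of follow-up are different periods. A test done before allocation cannot be an effect of the letters and fact sheets. It is expected equally often in both arms, so counting it shrinks the observed difference. For patients this is a practical matter: the Background says the guideline puts the first colonoscopy at diagnosis or, failing that, within six months of surgery, so it may be done before entry. For relatives, the index case's diagnosis date has no evident role as the start of an outcome window.

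There is also a data problem. The first survey looks back to about recruitment, so follow-up data alone cannot fill diagnosis-year 1. The stated rule therefore leaves two readings of the primary outcome, and an analyst could choose between them after seeing the data.

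**Working it through.** **1. The plan's own figures.** With 20% lost at each step, 600 × 0.8 = 480, 600 × 0.64 = 384 and 600 × 0.512 = 307 per group; the article gives 480, 380 and 300. Power for two proportions (two-sided 5%, assumed; n per group; difference d) is

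Φ{ [d − 1.96·√(2p̄(1−p̄)/n)] / √([p₁(1−p₁)+p₂(1−p₂)]/n) }.

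- Relatives, effective n = 400, d = 0.10: 0.844, 0.816, 0.809 and 0.813 at control rates 0.30, 0.38, 0.45 and 0.50. This reproduces the stated 80-85%.
- Index cases, n = 480, d = 0.10: 0.891 at a control rate of one third and 0.877 at one half. The stated 80% is met as a floor.

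The sample size arithmetic is not in dispute. The article gives no Aim 1 control rate. One third is the minimum assumed for Aim 2, one half is an upper value chosen here, and 0.23 to 0.38 is the Background range.

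**2. Share of year 1 before entry.** Let L be the months from diagnosis to entry, treating recruitment and randomization as one date. The share is L/12:

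| L (months) | 0 | 3 | 5 | 6 | 10 | 11 |
|---|---|---|---|---|---|---|
| Share of year 1 | 0% | 25% | 42% | 50% | 83% | 92% |

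L = 11 is 10 months to registration plus the 4-week doctor period. The later contact steps have no stated duration and could add more. The article does not give the distribution of L.

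**3. What the surveys cover.** Survey k covers diagnosis-months L + 12(k−1) to L + 12k. At L = 10 the windows are months 10-22, 22-34 and 34-46.

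- Year 1 (months 0-12): only months 10-12 are covered, 2 of 12.
- Year 2 (months 12-24): 10 months fall in survey 1 and 2 in survey 2.
- Year 3 (months 24-36): 10 months fall in survey 2 and 2 in survey 3.
- The other 10 months of survey 3 (36-46) lie in year 4.

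For any L up to 12, years 2 and 3 start at or after entry and lie within the three surveys' combined span. Assigning a test to the right diagnosis-year would need its date. The article describes doctor verification of timing for a random 10% of reported tests.

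**4. Illustration of dilution.** Assume that pre-entry tests are counted, that a 10-point gain accrues evenly over 12 months, and that everyone has the same lag. The year 1 difference is then 10 × (1 − L/12) points. Index power at 480 per group:

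| L | Difference (points) | Control 0.23 | Control 1/3 | Control 0.38 | Control 1/2 |
|---|---|---|---|---|---|
| 0 | 10.0 | 0.933 | 0.891 | 0.880 | 0.877 |
| 5 | 5.8 | 0.541 | 0.468 | 0.451 | 0.440 |
| 10 | 1.7 | 0.088 | 0.078 | 0.076 | 0.074 |

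**The case against.** Everything operational runs on the recruitment clock: follow-up times, recall period and sample size. One phrase departs from it and may be loose wording for follow-up time. That is plausible, but the phrase sits in the definition of the primary comparison for both populations and no other text overrides it.

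The follow-up surveys do not capture pre-entry tests. Such tests could enter only through the screening history taken at baseline, which nothing assigns to the outcome. If they are not counted, the power losses above do not describe the planned 12-month comparison. This stands, and it is why those figures are only an illustration.

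A diagnosis or surgery clock is needed to judge a patient's adherence. This also stands, but it settles whether a test was due, not when counting should begin.

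Four stronger readings are tempting, and the documents do not support them:

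- **Most of year 1 precedes the intervention.** This is true only for late entrants; the lag distribution is not given.
- **All three yearly comparisons are contaminated.** Years 2 and 3 hold no pre-entry time for lags up to 12 months.
- **The diagnostic colonoscopy is counted as an outcome.** The survey item asks about surveillance colonoscopy.
- **The result is biased towards one arm.** Randomization balances the lag in expectation.

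**Conclusion.** The point holds as a contradiction in the stated primary outcome, not as a detail left to another document. The analysis windows start at the index case's diagnosis, while data collection and power start at recruitment. Read literally, between 0% and about 92% of year 1 is pre-randomization time that the intervention cannot affect and the follow-up surveys do not cover; longer contact steps could raise the upper figure. Years 2 and 3 are affected only by misaligned boundaries for lags up to 12 months.

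The consequence is dilution of the year 1 comparison and a mismatch between data and analysis. Its size is unknown. The fall in index power to 44-47% at a 5-month lag (control rates of one third and one half) depends on counting pre-entry tests, even accrual of a 10-point gain, and a common lag. None of these is in the article. A reader should not infer that the trial has that power or that its sample size calculation is wrong.

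**What to change.** 1. Under Statistical analysis, Aim 1, start the outcome windows at randomization instead of the index case's diagnosis, assessed at the 12, 24 and 36 month surveys, for patients and relatives alike.
2. Count only tests dated after randomization. Use time since diagnosis or surgery and the baseline screening history only to judge whether a test was due and whether it was guideline-concordant.
3. State how people with no test due in a window are scored, including a patient who complied before entry, by one rule applied identically in both arms. Moving the origin does not settle this.
4. Reconcile Setting with Patient eligibility and recruitment on whether the 10-month limit applies to recruitment or to registration.

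The cost is one changed sentence, one added scoring rule and one aligned eligibility statement. The surveys already run from recruitment and the baseline interviews already record screening history, so no new survey round is needed. If randomization falls noticeably after recruitment, the first survey must separate tests done in that interval.

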## Background

Colorectal cancer (CRC) is among the most prevalent cancers worldwide and carries a substantial mortality and morbidity burden [1]. Five year survival ranges between 8% and 93%, depending on stage of disease [2]. Among people who have undergone surgical resection for CRC, surveillance colonoscopy is recommended at regular intervals to detect recurrence and metachronous cancers. In Australia, the National Health and Medical Research Council (NHMRC) clinical practice guidelines recommend that colonoscopy is performed at the time of diagnosis, or if this is not possible, within six months' of surgery, and then at an interval of 3-5 years [3]. Although NHMRC guidelines [3] have been available for some time, the level of uptake of the recommendations is uncertain. Australian studies have indicated that between 23%-38% of surveillance colonoscopies are in line with NHMRC recommendations [4,5].

Screening of first degree relatives (FDRs) of patients with colorectal cancer is widely recommended [6]. Evidence for the benefits of screening of first degree relatives of colorectal cancer patients come from prospective and retrospective cohort studies [5,7-9] and from a non-randomized study of relatives in a high risk familial setting, where there was a reduction in mortality from colorectal cancer in those accepting compared to those refusing screening [1]. The type of screening and recommended interval is dependent upon level of risk [3]. Current Australian guidelines classify risk levels for FDRs as shown in Table 1[3]. Recommended screening for each of these risk categories is as follows: *Risk level 1*: Faecal occult blood testing every second year from age 50 years and consider flexible sigmoidoscopy every 5 years. *Risk level 2: *Colonoscopy every 5 years starting at age 50 years or at 10 years younger than the earliest age of first diagnosis of bowel cancer in the family, whichever comes first. Flexible sigmoidoscopy and double contrast barium enema or CT colonography may be offered where colonoscopy is contraindicated. *Risk level 3*: Colonoscopy every one or two years for families with proven Hereditary Non-polyposis Colorectal Cancer (HNPCC) commencing at 25 years or 5 years before the earliest age of cancer diagnosis in the family, whichever comes first; annual screening for proven gene carriers or clinically affected members of Amsterdam-positive families.

**Table 1 T1:** Risk categories for colorectal cancer based on family history

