## Aims

The aims of this trial will be to:

i. Test the effectiveness of tailored print-based intervention to improve a) adherence to surveillance colonoscopy recommendations for people with bowel cancer b) adherence to bowel cancer screening guidelines among their first degree relatives.

ii. Examine how the identified cancer patients' and first degree relatives' socio-demographic characteristics, disease characteristics (for index case), risk category (for first degree relatives), intervention groups and providers' characteristics influence whether or not: a) colorectal cancer patients; and b) first degree relatives of colorectal cancer patients, are appropriately screened.

iii. Undertake a cost-effectiveness analysis of the intervention strategy by comparing the differential cost of an intervention and usual care conditions by changes in the quality-adjusted life years associated with each intervention.

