### FDR eligibility

First degree relatives of people with bowel cancer will be eligible to participate in the trial if they are a) aged 18 or older; b) English speaking; and c) able to provide informed consent. Those with a prior diagnosis of bowel cancer, Crohn's disease, or inflammatory bowel disease will be ineligible.

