### Recruitment of FDRs

Patients will be asked to provide the names and contact details of any living first degree relatives aged 18 or older. They will be asked to indicate which (if any) of their FDRs they are willing for the research team to contact about the study. A choice will be given regarding method of contact of FDRs. Option one will involve the patient being given a letter about the study which they can pass onto their relatives; while option 2 will involve the research team contacting the relative(s) directly by mail. Patients will be asked to seek their relatives' permission prior to selecting the latter option. Non responders for option one receive one reminder letter. The information pack will contain a cover letter, information statement about the study, and ask the person to contact the research team if they were interested in participating. If the index case has provided the relative's phone number, the letter will ask the relative to return a "do not contact" form within the next two weeks if they did not want a researcher to contact them about the study. FDRs that consent to being contacted will be telephoned and asked to participate in a brief screening interview to assess trial eligibility. Consenting eligible FDRs will complete a baseline computer-assisted telephone interview (CATI) which will include questions about age, gender, marital status, education, employment, knowledge about screening and prior screening history and future intentions of screening, use of complementary therapies, and quality of life. Quality of life will be assessed using the European Quality of Life Scale [12].

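### The primary (Aim 1) comparison is an unadjusted chi-square test, although baseline screening history, probably a strong predictor of the outcome, is collected and could be adjusted for at almost no cost

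*Protocol article*

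**What the plan says.** The Aim 1 outcome (Statistical analysis) is the proportion of index patients, and separately of FDRs, "who undertake screening/surveillance tests in line with NHMRC recommendations for their risk category in years 1, 2 and 3" after the index diagnosis. These proportions "will be compared between the two experimental groups using the chi-square test". No baseline covariate is named for this comparison. The section closes with "Analyses will be adjusted for clustering of relatives within index patients using Generalised Estimating Equations", which may extend to Aim 1 but deals with correlation within families, not with entry status.

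Screening history is available. The patient interview (Assessment of family history) records it, and the FDR interview (Recruitment of FDRs) covers "knowledge about screening and prior screening history and future intentions of screening". Statistical analysis names it only under Aim 2, which compares appropriately and inappropriately screened people on "Sociodemographic characteristics, screening history, risk status, concurrent engagement in alternative programs of surveillance and symptom status" and then fits a logistic model whose variables are chosen by p value.

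Two other places bear on the point. FDR eligibility excludes on disease history only ("Those with a prior diagnosis of bowel cancer, Crohn's disease, or inflammatory bowel disease will be ineligible"), so relatives who already follow the guideline can enter. Background gives the intervals. For patients, "colonoscopy is performed at the time of diagnosis, or if this is not possible, within six months' of surgery", and then every 3-5 years. For FDRs, faecal occult blood testing every second year at risk level 1, colonoscopy every 5 years at level 2, and colonoscopy every one or two years in proven hereditary families at level 3.

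**The concern.** When a recommended interval runs for several years, whether someone is appropriately screened at 12, 24 or 36 months depends heavily on when they were last tested. A level 2 relative who had a colonoscopy a year before entry is not due again for four years, which is beyond the 36-month follow-up. For a patient, a colonoscopy at diagnosis settles whether one is due within six months of surgery.

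Entry status is therefore probably among the strongest predictors of the Aim 1 outcome. A test that does not use it leaves the variation it explains in the error term. If the arms happen to differ in entry status, the difference passes into the estimate uncorrected. At stake is the precision of the main result, in a trial that plans 80-85% power for relatives.

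A related gap is that the article does not say how a person who was up to date at entry and has no new test is classified at follow-up.

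**Working it through.** **Inputs from the article (Sample size).** Effective FDR sample 400 per group at 12 months after a design effect of 2; target difference 10 points; 5% significance, taken as two-sided; stated power 80-85%. No control-arm rate is given for Aim 1. The only planning rate is the one under Aim 2, at least one third appropriately screened.

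**Reproducing the stated figure.** Pooled-variance chi-square power with 400 per group and a 10-point difference is 83.0% at a control rate of 1/3 and 80.9% at 0.45, the least favourable of the rates tried (0.20 to 0.50). Both agree with the stated range. For index cases, 480 per group with 10 points gives 89.1% and 87.4% at the same two rates, above the stated 80%. The point does not rest on a faulty sample size.

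**Assumed inputs (not in the article).** Share of FDRs up to date at entry q = 1/3. Follow-up adherence *hi* = 60-80% in them and *lo* = 15-20% in the rest.

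**Share of outcome variance explained by entry status.** With m = q·hi + (1 − q)·lo,

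R² = q(1 − q)(hi − lo)² / [m(1 − m)].

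**Power.** Φ(0.10 / √[2·m(1 − m)·(1 − R²)/400] − 1.96), with R² = 0 for the crude test.

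| hi, lo | m | R² | Crude power | Adjusted power |
|---|---|---|---|---|
| 0.60, 0.20 | 0.333 | 0.0356/0.2222 = 0.16 | 0.85 | 0.91 |
| 0.70, 0.20 | 0.367 | 0.0556/0.2322 = 0.24 | 0.84 | 0.92 |
| 0.80, 0.15 | 0.367 | 0.0939/0.2322 = 0.40 | 0.84 | 0.97 |

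First row in full: the crude standard error is √(2 × 0.2222/400) = 0.0333, so 0.10/0.0333 − 1.96 = 1.04 and power is 0.85. Multiplying the standard error by √0.84 gives 0.0306, so 0.10/0.0306 − 1.96 = 1.31 and power is 0.91.

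This simple formula uses one variance for both arms, so its crude figure is 1-2 points above the chi-square figure. The gain is what matters: roughly 5 to 13 points. If q is varied from 25% to 50% with the same adherence pairs, R² runs from 0.14 to 0.42.

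**Chance imbalance.** With q = 1/3 and 400 per group, the standard error of the between-arm difference in entry status is √(2 × 0.333 × 0.667/400) = 3.3 points, so the 95% range is about ±6.5 points. This applies the same design effect to entry status as to the outcome. A 5-point imbalance is 1.5 standard errors. It moves the crude difference by 0.05 × (hi − lo), which is 2.0, 2.5 and 3.25 points in the three rows, or a fifth to a third of the 10-point target.

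The imbalance shift and the power loss are two views of the same extra variance and should not be added together.

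No equivalent adjusted figure is given for patients, because the article offers nothing on how many had a colonoscopy at diagnosis. Their crude power is already higher, which leaves less to gain.

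**The case against.** **The planned test is valid.** Families are randomized centrally, about 600 index cases per arm. Chance imbalance is not bias, and the crude standard error already allows for it. This stands: the loss is one of efficiency.

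**The size rests on assumptions.** None of the adherence rates comes from the article, and a 5-point imbalance is not a typical draw (two-sided p about 0.13). This stands too, and the figures above are illustrations only.

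**Aim 2 may already cover it.** Aims lists "intervention groups and providers' characteristics influence whether or not" people are appropriately screened, and the Aim 2 logistic model can hold screening history as well. An arm effect adjusted for history is therefore possible. It is not guaranteed: entry at p ≤ 0.2 and backward removal at p ≥ 0.10 could drop either variable, so this is no pre-specified adjusted treatment effect.

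**Covariates belong in the analysis plan.** This is fair for matters on which a condensed article is silent, and the absence of any stated balancing of the randomization on screening history is not held against it. But for Aim 1 the article is not silent; it names the test.

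**Stronger readings that the text does not support.** A reader might infer that people up to date at entry count as successes in either arm throughout follow-up. The article does not say so. The outcome is worded as undertaking tests, and Follow up assessments asks only about the past 12 months, so on a literal reading such a person without a new test is not a success. At level 1, a test before entry would also fall due again within follow-up. A reader might also infer that the trial's real question is conversion of people who were not adherent. Aim i concerns adherence among patients and relatives overall, and the overall difference in proportions answers that.

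**Conclusion.** The point holds as a recommended improvement in precision, not as an error. Aim 1 commits to a crude comparison while a probably strong baseline predictor is collected and used only in Aim 2. The case for conditioning on entry status does not depend on how an up-to-date person without a new test is counted: prior testing predicts the outcome either way, as likely success or as likely non-success. That classification is nevertheless left open and should be settled.

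Under the assumed rates, FDR power at 12 months would rise from about 84-85% to about 91-97%. The gain shrinks towards nothing if few people are up to date at entry or if entry status predicts follow-up adherence only weakly. It would be wrong to conclude that the crude result is biased or that the trial is underpowered as stated.

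**What to change.** - Make the Aim 1 comparison a logistic model, fitted with GEE for FDRs, containing arm, baseline screening status and, for FDRs, risk category. For patients, the natural baseline term is whether a colonoscopy was done at diagnosis, if the interview supports it.
- Report the adjusted risk difference for the whole randomized sample, so that the estimate still answers Aim i on the scale used in the sample size section.
- Keep the crude comparison as a supportive analysis.
- Give the arm difference by baseline status as a pre-specified secondary subgroup analysis.
- State how a person up to date at entry with no new test is classified at each follow-up.

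The cost is a change of wording and slightly more analysis work, since logistic and GEE models are already planned. The main limit is data detail. The article says only that screening history is recorded, by self-report, and does not say whether test dates are held. Baseline status should be defined only as finely as the interview allows, and fixed before outcomes are compared by arm.
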